#### Statistical analysis

Due to the lack of studies that evaluate the effect of different loads of IMT, among them PThC, on the physical performance in recreational cyclists, we chose to carry out the statistical analysis considering the desired study effect size as proposed by Cohen [48]. Thus, the sample calculation was performed using GPower software 3.1.3 to determine the sample size, the mean effect size (*f* = 0.25, according to Cohen [48]) was used for the two-way mixed analysis of variance (ANOVA) and values of 0.05 for the type I probability error (α) and 0.80 for the type II probability error (power or β). Therefore, in order to ensure these pre-established conditions, at least 30 subjects should participate in this study.

All statistical analyses will be processed using the SPSS Statistics software 17.0 (SPSS Inc., Chicago, IL, USA). The level of significance will be set at *p* < 0.05. Normally distributed data will be presented according to the mean ± standard deviation and non-normally distributed data according to the median (interquartile range).

The Shapiro-Wilk test will be used to test for normal distribution and the Levene test for evaluation of homogeneity. A descriptive analysis of the three groups evaluated and then the paired *t* test will be performed on the following data: age, anthropometric evaluation, body composition densitometric analysis and blood test results.

The three groups will be compared considering the factors of group and training time, in terms of the variables PFT (FVC, FEV_1_/FVC, IC, ERV and MVV), RMS (MIP and MEP), CPET (VO_2PEAK_, VE, RR, OUES and VE/VCO_2_slope), cardiovascular variables (HR, CO, SAP, SV, total PVR) and metabolic variables (O_2_Hb, HHb, tHb and VO_2PEAK_), using two-way mixed ANOVA for parametric data analysis and for non-parametric data analsysis, the data will be mathematically transformed in order to normalize the data.

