### Subjects

Thirty recreational male cyclists, aged between 20 and 40 years, will be evaluated. They will be randomly divided into three groups: sham group (SG), PThC group (CPG) and 60% of the MIP group (60G). The groups will be formed by the randomization of the paired individuals with the same aerobic functional classification [31] and age group (subdivided into decades), using R software 3.0.2 to allocate the subjects.

The criteria used to select the participants will be as follows: male subjects aged 20 to 40 years old, apparently healthy, who have been practicing cycling for at least 6 consecutive months and at least 150 min/week (classified as active by the American College of Sports Medicine [32]). In addition, participants must not have abnormalities in the cardiovascular, respiratory, musculoskeletal or neurological systems, nor of other systems that make the proposed tests impossible. The exclusion criteria of the study are as follows: participants with electrocardiogram (ECG) changes (ischemia, overload, severe arrhythmias (such as ventricular tachycardia) and conduction disorders), both at rest and during the clinical exercise test, obesity (body mass index (BMI) >30 kg/m^2^), diabetes mellitus, hypertension, alterations in the results of laboratory tests, participants with respiratory muscle weakness (MIP<60% predicted [33]), smokers or former smokers with at least 1 year of interruption, alcoholics and users of illicit drugs or medication that may interfere with the results of the research and participants who have performed some type of IMT the last 12 months.

The participants will be recruited by electronic and printed media and by contact with subjects included in the database of the Laboratory of Cardiovascular Physiotherapy (LFCV) at the Federal University of São Carlos (UFSCar). Once identified, eligible participants will be invited to participate in the study and after they have accepted, they will carry out all the evaluations described subsequently and the type of training to which they are allocated.

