### Experimental protocol

The experimental protocol will take place over 13 weeks, as shown in Fig. 1. In the 1st, 5th, 9th and 13th weeks, the participants will be submitted to the following evaluations: CPET, RMS, iIME and constant load test (CLT). The PFT will be performed only in the 1st and 13th weeks of the study. The IMT will be carried out for 11 weeks. It is emphasized that the participants will continue doing the training during the reevaluation weeks. The aim of the reevaluations, which will be carried out in the 5th and 9th weeks of training, is to readjust the training loads and to follow the responses to the IMT.

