### Expected results

Among the scientific contributions from this project, the main one refers to adopting a new evaluation methodology (PThC) and prescription of IMT. It is expected that CPG will obtain better results than 60G and SG, such as obtaining a greater increase in workload (Watts) and peak oxygen uptake (VO_2PEAK_) in the CPET; higher MIP and iIME; decreased sensation of dyspnea and the sensation of peripheral fatigue, evaluated by the perception index to the physical effort of BORG/CR10 and delay in the activation of the inspiratory muscle metaboreflex both during the CPET and in the iIME.

Thus, it is expected that the use of IMT based on this new approach can increase the benefits derived from traditional methodology (IMT based on 60% of MIP); that it can provide subsidies on the best understanding of the physiological responses from its application; and that this new methodological approach can be used by health professionals as a new tool to evaluate and prescribe IMT, bringing more satisfactory results and greater physiological impact.

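### The test named and powered for the outcomes is an omnibus group-by-time ANOVA, which does not isolate the stated question of whether CPG beats 60G and sham

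*Protocol article*

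**What the plan says.** The Statistical analysis section compares the arms as follows: "The three groups will be compared considering the factors of group and training time", "using two-way mixed ANOVA for parametric data analysis", after transformation where the data are not normal. The same section ties the sample size to this ANOVA: f = 0.25, alpha 0.05, power 0.80, at least 30 participants. One other test is named ("A descriptive analysis of the three groups evaluated and then the paired" *t* test), but it covers only age, anthropometry, body composition and blood results. The article singles out no between-arm contrast and no visit as decisive.

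The question is stated elsewhere. The Aim section looks for a load that gives better results than traditional methods, and Expected results identifies the traditional method as 60% of MIP. It then says: "It is expected that CPG will obtain better results than 60G and SG", including a greater increase in workload and VO2peak. Both of these are listed under Primary outcome measures.

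The article does not write out the ANOVA layout. It follows from the Experimental protocol section: CPET and RMS are done in weeks 1, 5, 9 and 13, so those variables give three groups by four visits. For lung function the layout is three by two: "The PFT will be performed only in the 1st and 13th weeks of the study".

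**The concern.** The claim the trial wants to make is directional and pairwise: CPG above 60G, and CPG above SG, after training. A group-by-time interaction in a 3x4 layout has (3-1)(4-1) = 6 degrees of freedom and can be significant for any departure from parallel courses in any arm. The group main effect would not help either, because it averages in the baseline visit, where no training effect can exist.

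The easiest difference for this test to find may be active training against a 6 cmH2O sham. The Background section says that most studies with good results used 60% of MIP, so a working 60G arm is a realistic possibility. A significant interaction would then carry no information on whether PThC is the better load. The article hopes that health professionals will adopt PThC for prescribing training, so the comparison that supports adoption should be the one that is named and powered.

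**Working it through.** **Inputs from the article.** k = 3 groups, N = 30 (10 per arm if allocation is equal), m = 4 CPET visits, f = 0.25, alpha = 0.05, target power 0.80.

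**Assumed, because the article gives no values.** Visit correlation rho (0.5 to 0.9, equal for all pairs of visits), sphericity (epsilon = 1), linear build-up of gain from week 1 to week 13, and differences in between-subject SD units.

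**1. Reproducing the sample size.** For the interaction, lambda = f² × N × m / (1 − rho) = 0.0625 × 30 × 4 / 0.5 = 15, with df 6 and (30 − 3) × 3 = 81. The critical F is 2.213 and power is 0.809. At N = 27, lambda is 13.5 and power is 0.754. So 30 is the smallest balanced size that reaches 80%, and the 80% belongs to the omnibus interaction.

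**2. What f = 0.25 means when CPG = 60G > SG.** Let both active arms gain delta by week 13.
- The group-centred coefficients are −2/3, 1/3, 1/3, with mean square 2/9.
- The visit-centred coefficients are −1/2, −1/6, 1/6, 1/2, with mean square 5/36.
- Hence f = delta × sqrt(2/9 × 5/36) = 0.1757 × delta, and f = 0.25 requires delta = 0.25 / 0.1757 = 1.42 SD.

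At that effect and rho = 0.5 the interaction is significant in about 81% of trials, while the true CPG − 60G difference is zero and its contrast is significant in about 5%. At delta = 0.5 SD (f = 0.088) the interaction is significant in 13% / 29% / 57% at rho = 0.5 / 0.8 / 0.9. The 81% therefore depends on the large planned effect.

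**3. Power of the contrast that answers the question.** For the baseline-adjusted CPG − 60G difference at week 13, SE = sqrt(2/10 × (1 − rho²)) with 26 df. For 0.5 SD at rho = 0.5, SE = sqrt(0.2 × 0.75) = 0.387, the noncentrality is 0.5 / 0.387 = 1.29 and power is 24%. Results by rho:

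| rho | 0.5 | 0.7 | 0.8 | 0.9 |
|---|---|---|---|---|
| Power for 0.5 SD | 24% | 33% | 43% | 70% |
| Power for 0.8 SD | 51% | 67% | 82% | 98% |
| Difference with 80% power (SD) | 1.13 | 0.93 | 0.78 | 0.57 |

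Simulation gives slightly lower values for 0.5 SD: 23% / 42% / 67% at rho = 0.5 / 0.8 / 0.9.

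**4. Power for beating both arms.** If only CPG improves, by 0.5 SD, the probability that CPG − 60G and CPG − SG are both significant is about 12% / 27% / 53% at rho = 0.5 / 0.8 / 0.9.

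**5. Contrast against omnibus test.** Linear gain, equal correlation:

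| Scenario | rho | Interaction | CPG − 60G contrast |
|---|---|---|---|
| Only CPG gains 0.5 SD | 0.5 / 0.8 / 0.9 | 13% / 29% / 57% | 23% / 42% / 67% |
| Only CPG gains 0.8 SD | 0.5 / 0.7 / 0.9 | 29% / 50% / 96% | 50% / 67% / 97% |
| CPG gains 0.8, 60G gains 0.4 SD | 0.5 / 0.7 / 0.9 | 22% / 36% / 88% | 16% / 21% / 49% |

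In the last scenario the interaction has more power because it also picks up both active arms against sham. Restricted to CPG against 60G, a 3-df pairwise interaction has 10% / 14% / 37%, below the contrast's 16% / 21% / 49%.

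**The case against.** The strongest reply is that this is a condensed article. Pairwise tests after a mixed ANOVA are usually left to the full protocol or analysis plan, neither of which is shown. That stands as far as it goes: a reader might infer that no pairwise comparison will be made, or that a significant interaction alone will be reported as support for PThC, and the article says neither. But it does name the test and size the trial on it. A later list of post hoc tests would not change what the 80% refers to.

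Other stronger readings are tempting and are not supported:
- *The ANOVA is the weaker test.* Not in general. The order reverses when 60G also works, as shown above. Even for CPG against 60G alone, the contrast loses its lead with an early step gain at rho 0.9 (96.9% against 99.0% for the 3-df pairwise interaction, only CPG gaining 0.8 SD), or with a plateau gain and serially decaying correlation of 0.9 (69% against 75%).
- *The 81% is a false-positive rate.* It is correct power against a null hypothesis that is false, since sham does differ. The error would lie in reading it as evidence for CPG over 60G.
- *The sample size is wrong.* It agrees with the test it names.
- *Fatigue distorts weeks 5 and 9.* The article says "It is emphasized that the participants will continue doing the training during the reevaluation weeks", but it gives no spacing between sessions and tests, so differential fatigue is only a possibility.
- *The proposed analysis restores power.* It does not. Joint power for beating both arms (12% / 27% / 53%) is no better than that of the interaction (13% / 29% / 57%) when only CPG gains 0.5 SD.

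**Conclusion.** The point holds as a mismatch between the stated hypothesis and the test that is named and powered. The 6-df interaction can be significant in about 81% of trials with no CPG advantage over 60G, given f = 0.25, which is about 1.42 SD at week 13 under linear build-up, and rho = 0.5. The contrast that matters has about 23% to 70% power for 0.5 SD at 10 per arm, and beating both arms about 12% to 53% if only CPG improves, over rho 0.5 to 0.9. Correlation, sphericity, gain pattern and SD-scale effects are all assumptions. The reason to change is that the contrast answers the stated question; it is often, but not always, the more powerful test of CPG against 60G. Severity: should fix.

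**What to change.** Make the decisive primary analysis the CPG minus 60G difference at week 13 with its 95% CI, adjusted for the baseline value, by ANCOVA or as the week-13 contrast of a mixed model. Take CPG minus SG from the same model. Claim superiority over both arms only if both contrasts are significant; requiring both needs no split of alpha. Keep weeks 5 and 9 as supportive data on the course of response. State how VO2peak and W, both listed as primary, are handled: one of them as the single primary outcome, or both under a stated rule. State that the 80% power refers to the omnibus interaction, and give the power or detectable difference of the contrast at 10 per arm with the assumed correlation.

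The cost is a few sentences and a few lines of code, using data already scheduled for collection. The downside is that an effect seen only at week 5 or 9 becomes secondary. The change does not make 10 per arm adequate for a moderate CPG minus 60G difference; it makes that limit visible.

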### Expected results

Among the scientific contributions from this project, the main one refers to adopting a new evaluation methodology (PThC) and prescription of IMT. It is expected that CPG will obtain better results than 60G and SG, such as obtaining a greater increase in workload (Watts) and peak oxygen uptake (VO_2PEAK_) in the CPET; higher MIP and iIME; decreased sensation of dyspnea and the sensation of peripheral fatigue, evaluated by the perception index to the physical effort of BORG/CR10 and delay in the activation of the inspiratory muscle metaboreflex both during the CPET and in the iIME.

Thus, it is expected that the use of IMT based on this new approach can increase the benefits derived from traditional methodology (IMT based on 60% of MIP); that it can provide subsidies on the best understanding of the physiological responses from its application; and that this new methodological approach can be used by health professionals as a new tool to evaluate and prescribe IMT, bringing more satisfactory results and greater physiological impact.

## Discussion

Most systematic reviews [1, 3, 19, 49] that study the effects of IMT emphasize the need for studies with a controlled and randomized experimental design, following the guidelines of the Consolidated Standards of Reporting Trials (CONSORT) [50], and to establish training parameters that seek to achieve the best results for the population studied.

However, adapting this type of training to meet these guidelines becomes extremely complicated because of the need for this therapy to be used in a laboratory. Several experiments, also presented in these reviews [1, 3, 19], perform the training on average five times a day, or often with more than one session on the same day. Therefore, for the results of this research to be discussed considering the studies already published in the literature, we used the determination of the average training volume [51] of these studies, because this is an important parameter for determining training effectiveness, mainly resistance. Moreover, we divided the total time into three training days per week, the number of days also indicated by the American College of Sports Medicine [32], as the ideal time for performing physical activities, thus totaling 55 min of IMT on each day of training.

### Contributions to the area

This study will be important for physiotherapists, physical educators and other health professionals who work with physical exercise and training, as knowledge concerning the cardiovascular, respiratory and metabolic responses generated by IMT in recreational cyclists, using PThC and 60% of MIP, will enable these professionals to prescribe an IMT in a more suitable way for healthy active individuals. It will also help to encourage new studies that aim to promote greater gains in this population.

It is hoped that the results of this study will enable training performed with PThC to be used by health professionals as a new tool for assessing and prescribing IMT.

## Trial status

Status: participant recruitment is currently underway.

Recruitment began in May 2017.

Final recruitment will be December 2019.

## Abbreviations

60G: 60% of maximal inspiratory pressure group
AP: Arterial pressure
BMI: Body mass index
BORG/CR10: Subjective perception of effort scale
CLT: Constant load test
CO: Cardiac output
CONSORT: Consolidated Standards of Reporting Trials
CPET: Cardiopulmonary muscle test
CPG: Critical inspiratory pressure group
DFisio: Department of Physical Therapy
DPF: Differential path-length
DXA: Dual-energy x-ray absorptiometry
ECG: Electrocardiogram
EI: External intercostal
ERV: Expiratory reserve volume
FEV_1_: Forced expiratory volume in 1 s
FEV_1_/FVC: Relationship between FEV_1_ and FVC
FVC: Forced vital capacity
GET: Gas exchange threshold
HDL: High density lipoproteins
HHb: Deoxyhemoglobin
HR: Heart rate
IC: Inspiratory capacity
IME: Inspiratory muscle endurance
IMS: Inspiratory muscle strength
IMT: Inspiratory muscle training
iIME: Incremental inspiratory muscle endurance test
LDL: Low density lipoproteins
LFCV: Laboratory of Cardiovascular Physiotherapy
MAP: Mean arterial pressure
MEP: Maximal expiratory pressure
MIP: Maximal inspiratory pressure
MVV: Maximal voluntary ventilation
NIRS: Near infrared spectroscopy
NUPEF: Nucleus of Research in Physical Exercise
O_2_Hb: Oxyhemoglobin
OUES: Oxygen uptake efficiency slope
PFT: Pulmonary function test
PthC: Critical inspiratory pressure
PTh_MAX_: Maximal sustained respiratory pressure for 1 min
PVR: Peripheral vascular resistance
RCP: Respiratory compensation point
RME: Respiratory muscle endurance
RMS: Respiratory muscle strength test
RR: Respiratory rate
SG: Sham group
SPIRIT: Standard Protocol Items: Recommendations for Interventional Trials
SV: Stroke volume
SVC: Slow vital capacity
tHb: Total hemoglobin
T_LIM_: Inspiratory muscle endurance time
UFSCar: Federal University of São Carlos
UNILAB: Laboratory of Clinical Analysis at UNIMED
UNIMED: Cooperative medical system
USE: Health School Unit
VCO_2_: Carbon dioxide production
VE: Pulmonary ventilation
VE/VCO_2_ slope: Minute ventilation-carbon dioxide production slope
VL: Vastus lateralis
VO_2_: Oxygen uptake
VO_2PEAK_: Peak oxygen uptake
W′: Constant of curvature
W_LIM_: Maximal workload
